## Abstract

**Background:**

Previous studies have found that cancer patients undergoing chemotherapy can effectively manage their own symptoms when given tailored advice. This approach, however, may challenge patients with poor performance status and/or emotional distress. Our goal is to test an automated intervention that engages a friend or family member to support a patient through chemotherapy.

**Methods/Design:**

We describe the design and rationale of a randomized, controlled trial to assess the efficacy of 10 weeks of web-based caregiver alerts and tailored advice for helping a patient manage symptoms related to chemotherapy. The study aims to test the primary hypothesis that patients whose caregivers receive alerts and tailored advice will report less frequent and less severe symptoms at 10 and 14 weeks when compared to patients in the control arm; similarly, they will report better physical function, fewer outpatient visits and hospitalizations related to symptoms, and greater adherence to chemotherapy. 300 patients with solid tumors undergoing chemotherapy at two Veteran Administration oncology clinics reporting any symptom at a severity of ≥4 and a willing informal caregiver will be assigned to either 10 weeks of automated telephonic symptom assessment (ATSA) alone, or 10 weeks of ATSA plus web-based notification of symptom severity and problem solving advice to their chosen caregiver. Patients and caregivers will be surveyed at intake, 10 weeks and 14 weeks. Both groups will receive standard oncology, hospice, and palliative care.

**Discussion:**

Patients undergoing chemotherapy experience many symptoms that they may be able to manage with the support of an activated caregiver. This intervention uses readily available technology to improve patient caregiver communication about symptoms and caregiver knowledge of symptom management. If successful, it could substantially improve the quality of life of veterans and their families during the stresses of chemotherapy without substantially increasing the cost of care.

**Trial Registration:**

NCT00983892

## Background

Cancer is a prevalent problem that causes much suffering among patients and families. Most interventions to improve symptom control require patients to engage in activities such as managing medications, altering diets, or accessing outside resources that may be beyond their reach due to limitations in physical and mental functioning. Social network members inside and outside of the patient's household can assist with symptom monitoring, medication adherence, managing clinical encounters, and coping emotionally. Hogan et al found that among 92 studies meeting their entry criteria, 73 reported some benefit of social support provided by friends and families to patients with chronic conditions [1]. Unfortunately, cancer caregivers often lack the skills and resources they need to help the patient manage their treatment and the negative consequences of their disease and its management.

Few formal programs of supportive cancer care are designed to engage both patients and caregivers [2-11]. Among programs that have been evaluated, the majority of studies have had serious methodological flaws or limited evidence of effectiveness [8,12]. Northouse and colleagues examined the effects of three nurse home visits and two follow up nurse calls over four months to patients with prostate cancer and their spousal caregivers, with the goal of improving caregiver involvement, attitudes, coping, and quality of life [13]. Results showed some improvements in patient outcomes (better spousal communication and less uncertainty) and multiple improvement in caregiver outcomes (higher quality of life, self-efficacy, and communication; less symptom distress and negative appraisal of caregiving), with some effects sustained to 12 months follow-up. Given and colleagues tested the effects of a cognitive behavioral intervention administered by a nurse via telephone to assist patients undergoing chemotherapy to manage symptoms and assist caregivers to become involved in supporting symptom management. Patients receiving the intervention reported 34% and 30% lower symptom severity at 10 and 20 weeks, respectively [11]. Caregivers did not report any change in their involvement or distress, and some caregivers reported increased depressive symptoms [14,15].

The current protocol describes an ongoing randomized trial designed to address these gaps in the literature by developing and evaluating an intervention that provides cancer patients and caregivers with the information they need to make effective management decisions, decrease symptom burden, and improve patient and caregiver outcomes. The study was funded by the VA Health Services Research and Development Service and began October, 2009. The trial will be completed in August 2013.

The intervention uses a Web-enabled program to alert caregivers of patients' symptoms and provide them with a framework for identifying problems, receiving structured advice, and following up to assist the patient in manage symptoms while receiving chemotherapy. Specifically, the intervention includes weekly, automated telephonic symptom assessment with self-management support calls to patients paired with Web-based caregiver alerts that include customized advice. The study will enroll 300 patients with solid tumors undergoing chemotherapy identified from two Department of Veterans Affairs (VA) outpatient oncology clinics. Patients are recruited along with an informal caregiver willing to play a limited role in assisting the patient with symptom management. The impact of the intervention will be evaluated relative to a control arm in which patients receive automated telephonic symptom assessments and self-management advice without any involvement of their identified caregiver. Thus this is one of the few rigorously designed interventions that tests the value added impact of engaging informal caregivers in symptom management for patients with cancer. Specific study hypotheses are as follows:

*Hypothesis 1a: Patients receiving automated telephonic symptom assessment and management advice, with Web-based feedback to inform and engage a caregiver, will report less frequent and less severe symptoms at 10 and 14 weeks when compared to patients receiving automated telephonic symptom assessment and management advice alone. Intervention-group patients will also report better physical function, fewer outpatient visits and hospitalizations related to symptoms, and greater adherence to chemotherapy*.

*Hypothesis 1b. The effect of the intervention on symptom severity, physical functioning, and utilization of services will be partially mediated by improved patient self-efficacy and actualized social support*.

*Hypothesis 2a: Caregivers receiving the intervention will provide significantly more social support to patients at 10 and 14 weeks as evidenced by increases in patient-reported measures of social support when compared with caregivers who do not receive the intervention*.

*Hypothesis 2b: Caregivers receiving the intervention will report lower perceived caregiving burden and distress compared to caregivers in the comparison group*.

### Theoretical Model

The study is based on the stress-coping model which identifies the processes influencing quality of life in patients with cancer (Figure 1) [16,17]. According to this model, when a cancer patient develops a need-e.g. a symptom-s/he is able to address the need to the extent that s/he is self-efficacious and functional. The system we are evaluating improves patient self-efficacy by providing patients with tailored information about what they can do to feel better. By activating an informal caregiver to support the patient, there is an additional source of information and encouragement to promote the patient's self-efficacy. How the patient uses the information provided during automated telephonic interactions determines his/her quality of life, ability to comply with chemotherapy, and utilization of services. The proposed intervention serves not only to improve patient access to information, but also to increase the speed of information transfer between patient and caregiver.

**Figure 1 F1:**
[figure not shown]
**Depiction of theoretical model**. CG = caregiver; CR = care recipient.

### Intervention Components

#### Automated Telephonic Symptom Assessment (ATSA)

ATSA is an automated telephonic system that calls patients at home to collect their symptom ratings via responses to recorded queries using their telephone's touchtone keypad. ATSA's questions consist of items from the MD Anderson Symptom Inventory modified for the telephone and validated in prior cognitive-behavioral studies of symptom management [15,18-21]. The ATSA system was developed based on prior research showing that patients with cancer and other serious chronic diseases can and will report reliable information during automated assessment calls, and that such calls may improve their self-care and health outcomes [22-25]. The duration and intensity of the intervention is premised on past work that suggesting that ATSA's benefits peak at 10 weeks [26].

The ATSA system calls patients weekly and asks them to rate the frequency and severity of eight core symptoms: pain, distress, fatigue, insomnia, nausea, poor appetite, dry mouth, and constipation. The choice of core symptoms is based on prior work by Given and colleagues showing that among patients undergoing chemotherapy, 85% experience at least one of these symptoms [11]. Patients are asked how many days during the last week they have experienced each symptom. When patients report a frequency of once per week or greater, the ATSA prompts patients to rate the severity of that symptom on a scale of 0 to10.

During the automated telephonic interaction, the ATSA system gives targeted advice for self-management depending upon the severity of the symptoms reported by the patient. For a severity of three or less, ATSA gives no advice. For a severity greater than three, ATSA refers the patient to the appropriate section of a printed "Symptom Management Toolkit" which the patient receives upon study enrollment. Details about the Toolkit are provided below. When a symptom is reported with a severity of seven or higher, ATSA not only refers the patient to the appropriate section of the Toolkit, but also recommends that the patient contact his/her VA oncology provider. The cut points of 3 and 7 were chosen based on severity scores shown to have similar levels of interference with functioning among patients with cancer [21]. If an ATSA call is not completed at the designated time, the system automatically attempts a repeat call twice at 15 minute intervals. If not completed that day, another call is attempted on the next day at the same time. ATSA stores data on patients' symptom scores as well as the number of attempted call assessments, date/time stamps for all call attempts, and the number of missed call attempts for the purposes of evaluating service usability.

#### The Symptom Management Toolkit

The Toolkit is a printed, patient guide for managing symptoms commonly seen in cancer, organized by symptom in a question/answer format. The Toolkit was developed by [name] and [name] for use in ATSA. Strategies included in the Toolkit are based on recommendations from the National Comprehensive Cancer Network, National Institutes of Health, Oncology Nursing Society, and other groups of nationally recognized experts, supplemented by literature gained from extensive reviews of MEDLINE, CINAHL, PsychInfo, and PubMed for evidence-based interventions [27-29]. The Toolkit has been successfully used by both patients and in-home caregivers to manage symptoms in patients undergoing chemotherapy in five prior studies [11,14,15,20,30].

#### Cancer CarePartners

Cancer CarePartners is a Web based resource that draws information from the ATSA calls and uses that as well as a detailed set of caregiver support tools to provide caregivers with assistance in decision-making and instrumental assistance to improve patients' symptom management. Following each of patients' ATSA assessments, Cancer CarePartners alerts the caregiver about the patient's symptoms and helps the caregiver develop strategies for addressing the patient's needs. Cancer CarePartners was designed based on the problem-solving conceptual framework established by D'Zurilla and Nezu for family caregivers of people with physical illnesses [31]. In this framework, problem solving is seen as the rational and systematic construction of a solution through the use of four specific problem solving skills: 1) problem definition and formulation, 2) generation of alternatives, 3) decision making, and 4) solution implementation and verification. Table 1 summarizes how Cancer CarePartners develops these four skills in cancer caregivers; screenshots are shown in Figure 2.

**Table 1 T1:** Cancer CarePartners Web site components and caregiver skills targeted.

**Targeted caregiver skills**		**Web site components**
		
Problem definition & formulation	**→**	Upon logging into the Cancer CarePartners web site, the caregiver sees a depiction of the patient's last symptom scores using horizontal thermometers (Figure 1a). Symptoms are presented in order of severity, with the most severe symptoms displayed at the top of the screen. Caregivers can select a symptom to access additional information about the symptom's cause and management (Figure 1b). Caregivers also can access reports showing trends in each symptom over time.
		
Generation of alternatives	**→**	The Web site asks caregivers to identify one symptom that they would like to help the patient work on that week. Upon choosing the symptom, the caregiver sees a list of recommendations suited to the patient's last assessment (Figure 1c). Advice is grouped by its targeted domain: namely, activity (i.e. exercise), communication, diet, medication, and mood. For example, if the patient reported dry mouth and the caregiver chooses to address that symptom with additional self-care assistance, they may receive advice such as "make sure the patient has a water bottle at his/her side at all times."
		
Decision making	**→**	Caregivers are asked to commit to trying three to five tasks for the week from the list of recommendations. To help caregivers make informed decisions about which recommendations to adopt, the Web site describes each task's purpose and what is involved, and provides examples for how to accomplish it.
		
Solution implementation & verification	**→**	After committing to 3-5 tasks, caregivers can print a list of their choices, or "Task List, " for future reference (Figure 1d). The next time the caregiver logs into the website, she is asked which of the tasks she attempted and whether the recommended action was helpful (Figure 1e). In addition to allowing caregivers to self-monitor the outcomes associated with their assistance, the data allow the investigative team to determine uptake of specific advice offered by Cancer CarePartners and caregivers' perceptions about its benefit.

**Figure 2 F2:**
[figure not shown]
**Screen shots of Cancer CarePartners Web site**.

## Methods

The intervention's efficacy is being evaluated using a randomized, controlled trial among patients undergoing a course of chemotherapy at two Department of Veterans Affairs (VA) oncology clinics located in Ann Arbor, MI and Fargo, ND. Three hundred patients with solid tumors undergoing chemotherapy and reporting at least one core symptom at a moderate level are being assigned to either 10 weeks of weekly ATSA contacts or 10 weeks of weekly ATSA contacts plus caregiver alerts and access to the Cancer CarePartners website. The duration and intensity of the intervention is premised on past work suggesting that ATSA's benefits peak at 10 weeks [11].

The goal of the study is to determine if, when compared to a comparison group receiving ATSA alone, patients who receive ATSA and whose caregivers receive access to Cancer CarePartners will report: significantly less total symptom severity; and secondarily improved physical functioning, adherence to chemotherapy, and more appropriate utilization of health services at 10 weeks. The study also will determine whether caregivers provide more social support and report less caregiver burden and distress.

Patients and caregivers will be surveyed at intake, 10, and 14 weeks. Further, we will track patient participation with ATSA and (in the experimental arm) caregiver use of the Website and social support provided, allowing for indicators of intervention dose to be incorporated into our analyses. Finally, all patients will receive routine oncology, hospice, and/or palliative care.

### Eligibility

Study patients must be 21 years or older, cognitively intact, English speaking, able to hear, and able to use the phone. They must have home access to a touch-tone telephone. They must have a solid tumor; for example, prostate, lung, colorectal, breast, non-Hodgkin lymphoma, or head/neck cancer. Patients may have new or recurrent disease in early or late stage. All patients must be within 10 weeks of initiating chemotherapy and, if they are being treated for recurrent disease, must have experienced a treatment free interval of 10 weeks between the new and past treatment. Patients may live alone or with others, with or without an in-home caregiver. Patients are excluded if they have been diagnosed with a hematologic malignancy or their treatment regimen involves bone marrow transplantation because such patients' symptom profiles differ from those of other cancer patients. Also, patients will be excluded if they (a) have untreated mental illness or cognitive impairment limiting their ability to participate with ATSA, (b) cannot identify at least one potential consenting caregiver, (c) are institutionalized or enrolled in hospice prior to enrollment, or (d) plan to discontinue receiving the majority of care from one of the study sites during the follow-up period.

For the purposes of this study, a potential caregiver *is defined as a person living inside or outside of the patient's household who has at least monthly contact with the patient, either by phone or in person, and is willing to help the patient manage his/her symptoms*. S/he must be 21 years or older, cognitively intact, English speaking, and able to hear and speak English for telephone interviews. S/he must have access to a telephone and computer with a high-speed Internet connection.

Caregivers need not be providing direct care prior to the study; indeed, a major motivation for this intervention is that many well-intentioned friends and family members would be willing to provide more cancer support, but currently do not do so because there is no structure in place to make that possible. Caregivers will be excluded if they, themselves, are on active treatment for cancer. They will also be excluded if they have poorly controlled mental illness, moderate cognitive impairment, or are unable to be interviewed by telephone.

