### Recruitment & Randomization

Study staff review the schedules of participating chemotherapy infusion clinics weekly to identify potentially eligible patients. The list of potentially eligible patients is provided to staff oncologists for their approval prior to attempting recruitment.

Eligible patients are approached by research assistants after their second week of chemotherapy. Research staff explain the study to them, screen for eligibility, offer enrollment, and obtain informed consent. Patients agreeing to participate are asked to identify at least four potential caregivers using an algorithm based on the Norbeck Social Support Scale to determine the ranking of choices according to their involvement in the patient's life [32,33]. Research assistants then obtain contact information for the potential caregivers. Potential caregivers are recruited by research assistants by phone or in person if they accompany the patient to clinic. The research assistants explain the study, screen for eligibility, and obtain written informed consent. When a potential caregiver declines participation in the study, the research assistants contact the remaining potential caregivers on the list following the ranking provided by the patient. If no potential caregiver consents to participate, the patient is excluded from the study.

Patient participants are asked to identify preferred calling times for their ATSA calls. In addition, they are instructed on the use ATSA and rehearse an ATSA symptom assessment with the research assistant while in clinic. All patient participants are told to contact the project manager if they have any questions during their participation in the study and are given the telephone number for their respective oncology clinic for clinical issues not related to the study or when advised to do so by ATSA.

Basic sociodemographic and clinical data are kept on patients and caregivers who are ineligible for or refuse enrollment in order to understand the reach of the intervention in the broader population of eligible patients. In particular, we will describe the extent to which the requirement of caregiver Internet access serves as a barrier to recruitment among economically disadvantaged or rural patients.

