#### ATSA

ATSA tracks call attempts, call outcomes (completed vs. incomplete), and reported symptom scores. The number of completed calls relative to call attempts will be used to describe patient uptake of the intervention as well as the dose received.

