### Description of Patient Measures

#### Summed symptom severity score

(source: patient baseline, 10 week, and 14 week surveys). A summed symptom score will be generated based on the sum of symptom severity scores (scored 0-10) across the 8 core symptoms.

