### Quality control

Research assistants rehearse an ATSA call with every patient participant at the time of enrollment. They review call data from ATSA regularly to identify patients who do not respond to scheduled calls. When patients do not respond to multiple ATSA attempts over 48 hours (at any period throughout the 10 weeks of the trial), research assistants contact them to determine the reason; reasons for non-compliance are tracked. Support is offered to patients whose reason for noncompliance relates to technical issues.

Similarly, for the first 4 weeks on the study, caregivers' Web logs are reviewed to identify caregivers who either have not been able to sign-in or create a task list. Research assistants contact caregivers whose Web logs indicate noncompliance and call caregivers to identify the cause. Depending on the reason for the difficulty, research assistants offer to guide the caregiver by telephone during their next online session. Research assistants track all reasons for noncompliance with the website.

Patients and caregivers are not permitted to use ATSA or the website until the baseline survey is completed. Data is entered into a clinical data tracking system that alerts staff of survey due dates and incomplete data. The date the baseline survey is completed determines the dates for the 10 and 14 week surveys. Up to 10 attempts are made to contact each subject or caregiver for scheduling an interview. Abbreviated versions of all interviews are available for patients who have difficulty completing the entire survey. Patients and caregivers receive a $15 gift card for each survey they complete. Monthly updates with comments on completeness of data are maintained and reviewed by the Project Manager.

The success of randomization is monitored quarterly by comparing the demographic and clinical characteristics of patients across study arms. Clinical staff is blinded to the assignment arm, as are the analysts examining the data.

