#### Primary Analytic Strategy

The primary effect of the intervention will be determined using data obtained at 10 weeks, and the sustained effect will be determined using data obtained at 14 weeks. Cross group comparisons will be made based on an intention-to-treat basis. We will also test the hypotheses with a longitudinal design by fitting a linear mixed-effects modelor a generalized linear mixed effects model to estimate effect averaged over 10 and 14 weeks, adjusting for potential within-person correlation and baseline values of the outcome variables [15].

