#### Hypothesis Testing

We will compare summed symptom scores at 10 weeks between the control and intervention groups using a multiple regression model. The model will include a dummy variable for study group assignment as the main independent variable and will be adjusted for baseline symptom scores. While we do not expect the groups to be unbalanced with respect to other potential predictors of the outcome, we will adjust for these if randomization is not fully successful. The parameter estimate of the group assignment dummy variable and its statistical significance will estimate and test for the outcome difference between the two study groups at week 10, adjusting for baseline values of the outcome. A similar approach will be used to test the intervention effect on secondary outcomes (namely physical functioning, service utilization, and chemotherapy adherence). To determine if there is maintenance of the intervention effects on each outcome, we will use a similar regression model using the corresponding measurements at week 14, and a longitudinal model for the outcomes at 10 and 14 weeks.

Our analytic approach for testing Hypothesis 2 will be similar to that described above. We will use multiple regression models to compare group differences in patient-reported social support scores as measured by the Inventory of Socially Supportive Behaviors at 10 weeks, adjusting for baseline values of the ISSB [38]. The model will include a dummy variable for study group assignment as well as the baseline value of the ISSB scores, and the parameter estimate of the dummy variable will estimate the intervention effect on caregivers at 10 weeks. A similar approach will be used to test the intervention effect on caregiver burden and distress.

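### The primary week-10 survey falls at about chemotherapy weeks 12 to 20 with no fixed adjustment for that timing, and patients lost before it contribute no outcome value although weekly symptom scores are held

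*Protocol article*

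**What the plan says.** **Entry and timing.** Eligibility states: "All patients must be within 10 weeks of initiating chemotherapy". Recruitment & Randomization adds: "Eligible patients are approached by research assistants after their second week of chemotherapy". Quality control sets the clock: "The date the baseline survey is completed determines the dates for the 10 and 14 week surveys". No section ties a survey to the chemotherapy course or requires that chemotherapy still be under way at week 10.

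**Primary analysis.** Primary Analytic Strategy: "The primary effect of the intervention will be determined using data obtained at 10 weeks". Hypothesis Testing: "We will compare summed symptom scores at 10 weeks between the control and intervention groups using a multiple regression model", adjusted for the baseline score. Other predictors enter only if the arms turn out to be unbalanced; Baseline Analysis is conditional in the same way. The minimization factors are cancer type (lung or other) and caregiver location.

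**Source of the outcome.** Summed symptom severity score: "source: patient baseline, 10 week, and 14 week surveys). A summed symptom score will be generated". Missing Data names the 10- and 14-week assessments as the longitudinal outcome values, with baseline as a covariate.

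**Weekly data.** The intervention description says: "The ATSA system calls patients weekly and asks them to rate the frequency and severity of eight core symptoms". Both arms receive these calls for 10 weeks and the scores are stored. The article gives the stored ATSA data a role in judging usability, triggering caregiver alerts and weekly safety review. For call counts, as distinct from symptom scores, it says: "The number of completed calls relative to call attempts will be used to describe patient uptake of the intervention as well as the dose received".

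**The concern.** The trial asks whether informing a caregiver helps a patient manage symptoms while receiving chemotherapy. The primary assessment is one survey whose position in the chemotherapy course varies by about eight weeks between patients. If symptom level depends on that position, the variation adds between-patient noise to the primary comparison and blurs what the week-10 estimate describes. The adjustment rule does not help: a prognostic variable that happens to be balanced is never adjusted for, although adjustment would still improve precision.

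The second issue is information left out of the analysis. The protocol expects 25% attrition and lets patients who enter hospice come off study, so loss may be related to illness. A patient lost before week 10 has no outcome value in any planned model, even with several weekly scores on file. Those scores are what would make a missing-at-random assumption more credible.

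**Working it through.** **1. Position of the surveys in the chemotherapy course.** Inputs: earliest approach at about week 2 (Recruitment & Randomization), latest entry at week 10 (Eligibility), surveys 10 and 14 weeks after baseline (Quality control).

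- Primary survey: 2 + 10 = 12 to 10 + 10 = 20, a spread of 8 weeks.
- Second survey: 2 + 14 = 16 to 10 + 14 = 24.

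These are approximate outer limits. Caregiver recruitment and the baseline survey follow the approach to the patient, and the distribution of entry times is not given.

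**2. What a fixed covariate would give.** If r is the partial correlation between weeks since chemotherapy start and the week-10 score, given baseline, adjustment multiplies the residual variance by 1 − r². The article gives nothing from which to set r, so the gain cannot be sized.

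**3. Patients without an outcome value.** The plan's own inflation reproduces: 224 / 0.75 = 298.7, or 299, against a goal of 300. Expected attrition is 0.25 × 300 = 75 dyads. That is an upper limit for losses before week 10 at the planned rate, because some losses will come later and some will be of the caregiver. In a model with baseline as a covariate and outcomes only at weeks 10 and 14, a patient lost before week 10 adds no outcome row. A pattern mixture model can bring such patients in only through assumptions about their unseen values.

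**4. Would a weekly mean be more precise?** No correlation is stated, so I assume one common correlation ρ and equal variances, with baseline adjustment. In units of the variance of one score:

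- single week-10 score: 1 − ρ²
- mean of 10 weekly scores: (1 + 9ρ)/10 − ρ²
- standard error ratio: the square root of the second over the first

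Power is for 112 per arm, 0.33 SD at week 10, two-sided 0.05. In the linear case the effect rises in equal steps to week 10, so its average is (0.1 + 0.2 + … + 1.0)/10 = 0.55 of the week-10 effect.

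| ρ | Variance, single | Variance, weekly mean | SE ratio | Power, single survey | Power, weekly mean, constant effect | Power, weekly mean, linear build |
|---|---|---|---|---|---|---|
| 0.4 | 0.84 | 0.30 | 0.598 | 76.9% | 99.5% | 69.8% |
| 0.5 | 0.75 | 0.30 | 0.632 | 81.4% | 99.5% | 69.8% |
| 0.6 | 0.64 | 0.28 | 0.661 | 87.0% | 99.7% | 72.8% |
| 0.7 | 0.51 | 0.24 | 0.686 | 93.3% | 99.9% | 79.2% |

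The weekly mean does better only if its average effect exceeds the SE ratio, about 60 to 70% of the week-10 effect. The linear 55% falls short at every ρ shown.

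The first call precedes any alert and should be left out. With nine calls the variance is (1 + 8ρ)/9 − ρ² and the ratios are 0.604, 0.638, 0.667 and 0.691. An effect of zero at call 1, rising in equal steps to full at call 10, averages (1 + 2 + … + 9)/(9 × 9) = 45/81 = 0.556 over calls 2 to 10. The conclusion is the same.

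I use 112 per arm only as the planned number of completers. Without baseline adjustment it gives 69% power at 0.33 SD two-sided, and 80% would need 145 per arm. That is a separate matter, and nothing here depends on it.

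**The case against.** Week 10 is a reasoned choice. It is the end of the intervention, and the article cites past work suggesting that the benefit of ATSA peaks then. That stands, and it is why the primary time point should stay. It also weakens the precision argument, since an effect that builds towards week 10 is the case in which the weekly mean loses. A reader might infer from the SE ratios that the weekly series would cut the standard error by 31 to 40% and make a better primary outcome. The documents do not support that: the correlations are assumed, the survey is an interview while ATSA is a touchtone call that asks severity only if the symptom occurred that week, and the gain depends on the time course of the effect.

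ATSA is also part of the intervention. Only intervention-arm caregivers see the scores, so reporting may differ by arm, and a separate survey avoids this. That also stands, and it limits the weekly scores to a supporting role.

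Finally, timing is a baseline variable, the plan adjusts for observed imbalances and allows other covariates, and further secondary outcomes may sit in an analysis plan that is not shown. This stands in part. No complaint can rest on silence about additional analyses. But the article does fix the source of the symptom score, the outcome times in the models, and the condition for adjusting.

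**Conclusion.** The point holds as a weakness in precision, interpretation and missing-data handling. The primary survey falls at about chemotherapy weeks 12 to 20, timing is adjusted for only if imbalance is seen, and up to 75 of 300 dyads at the planned attrition could lack any outcome value while weekly scores are on file for some of their follow-up.

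Two stronger readings are tempting. One is that varying timing biases the treatment comparison. It does not: timing is fixed before allocation and balanced in expectation, although it is not a minimization factor. The other is that many patients will have finished chemotherapy by the primary survey. Nothing rules this out, but no course length or entry distribution is given, so the number is unknown. The value of the fixed covariate rests on timing being prognostic, which is plausible but not shown in the article.

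**What to change.** Keep the baseline-adjusted week-10 survey score as the primary outcome, and make two changes before the arms are compared.

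1. Add weeks since chemotherapy start at baseline as a fixed covariate in the week-10, week-14 and longitudinal models, whether or not imbalance is observed. It should be known from the eligibility check.
2. Prespecify weekly ATSA summed severity during the intervention, from the second call on, as a supporting secondary outcome in a likelihood-based repeated-measures model adjusted for baseline. Use the weekly scores as auxiliary information in the missing-data analysis for patients lost before week 10.

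State the limits with the second change: reporting may differ by arm, calls may be missed or suspended during hospital stays, and the mode differs from the survey. Do not present it as a sure gain in power.

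A subgroup by whether chemotherapy was planned to continue to week 10 should not be added unless planned duration is taken from notes written before randomization. The chart review takes place at week 14 or after withdrawal or death, and the article does not say that the recommended duration is fixed as of baseline.

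The cost is analysis-plan wording and programming. No new contacts or data collection are needed.
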